### Resin infiltration group

#### Placebo therapy

Children will receive sterile water application, as a placebo, maintaining the same steps used for application of SDF.

#### Intervention

Local anesthesia and adaptation of the rubber dam and clamps will be performed. The adjacent tooth will be protected by plastic or metal strip. Hydrochloric acid 15% will be applied on the lesion for 120 s. Then, after washing and air-drying, the lesion will be dehydrated by applying 95% ethanol, followed by air-drying. The resin infiltrant will be applied on the lesion for 120 s and light-cured for 40s. Resin will be reapplied for 30s and light-cured again. All products used in resin infiltration are included in a specific kit commercialized by the manufacturers for this purpose (Icon® – Dental Milestones Guaranteed – DMG, Germany). At the end, patients and their parents will also receive instructions for daily flossing as described above.

### Control group

#### Placebo therapy

Children will receive sterile water application, as a placebo, maintaining the same steps of used for application of SDF and for resin infiltration, without local infiltration anesthesia and clamp.

The active treatment in this group will be only instruction for daily flossing as described above.

### Primary outcome

A single trained, calibrated, and blinded examiner ([name]) will assess caries lesions progression by direct visual exam using ICDAS and an adjunct index to assess caries lesion activity status [23]. The ICDAS score and the activity status will be assessed after tooth separation for at least 48 hours. The main outcome considered will be caries progression to evident dentine cavitated caries lesion. Bitewing radiographs will be taken to evaluate possible caries progression into dentin according to Ekstrand et al. [15]. The progression detected by radiographs or by ICDAS scores transition, as well as changes in the caries lesion activity status, will be considered as possible surrogate outcomes.

### Second outcome measurements

Patient discomfort will be assessed immediately after the sequence of treatments have been performed. Wong-Baker Faces Scale [24] will be applied to measure patient discomfort. The scale presents six figures from the happiest face to the unhappiest face in order to estimate discomfort level after procedure. An external examiner ([name]) will instruct the child/adolescent to indicate which face represented his/her feeling regarding the procedures [20, 21].

We will also investigate parents’/guardians’ satisfaction regarding the patient’s treatment. The adolescent will be also asked to score his/her satisfaction. The assessments will be done in the first and last follow-up visits (1 and 24 months) and the examiners will ask them not to restrain from answering their actual opinion. Parents and adolescents should rank their satisfaction as: 0 – excellent; 1 – good; 2 – acceptable; 3 – bad [25].

Costs analyses will be performed based on the direct and indirect costs of the procedures. All appointments will be timed by an external examiner ([name]). The number of expected and unexpected visits for each patient and the procedure performed in each session will be recorded, as well as their respective duration. To calculate the direct costs, the costs of materials used will be searched [26, 27]. These values will be inferences of market value obtained by a mean cost practiced by different dental stores. These data will be updated during the study. For the calculations, indirect costs will also be considered, as used in previous studies [26, 27].

Based on data collected for efficacy and cost analysis, we will propose a specific model for cost-efficacy estimation, based on previous published strategies [28].

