**Methods/design:**

This is a randomized clinical trial, double-blinded, placebo-controlled study. Children/adolescents presenting at least one approximal initial caries lesion in primary molars/permanent premolars and molars will be included. Surfaces with advanced dentine lesions identified by radiography and participants who refuse to participate or present negative behaviors will be excluded. A minimum sample size of 504 surfaces will be required for each subgroup. Individuals will be randomly allocated in three groups of interventions: SDF, resin infiltration, and control group. Depending on the allocation, the patients will receive the active treatment and respective placebo therapies. All patients will be oriented to daily flossing the included surfaces. Our primary outcome will be caries progression by clinical and radiographic examinations. Appointments will be timed and costs of materials will be considered to calculate cost-efficacy. Patient discomfort will be assessed after interventions. Parent and patient satisfaction with the treatment will be collected after treatment and in the last follow-up visit. Individuals will be assessed at 1 and 3 months after treatment to evaluate dental biofilm and at 6, 12, and 24 months to assess caries progression by visual examination and/or radiography. Multilevel analyses will be used to verify if the type of treatment influenced on the tested outcomes. Costs will be compared and analyses of cost-efficacy will be performed. Poisson analysis will test the association between intervention and reported discomfort and satisfaction.

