**Discussion:**

Our hypothesis is that SDF is the most cost-efficacious option from all tested interventions. If our hypothesis is confirmed, the use of SDF in private and public contexts could represent an easier and effective option in the treatment of enamel approximal caries in children/adolescents.

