### Random allocation

The three parallel groups of interventions are defined as SDF, caries resin infiltration, and control group (exclusively flossing instructions).

The individuals will be randomly allocated to each group according to a sequence obtained in appropriate statistical software (Medcalc software version 12.4.0.0, Ostend, Belgium). The generated sequence will be distributed in opaque and sealed envelopes, which will be opened by the operators ([name]) only at the moment of the interventions.

All individuals enrolled in the study will receive in each included surface the active intervention, the placebo therapy, and instruction for daily flossing this specific surface. When the active treatment is exclusively flossing, two placebo therapies will be used, as described below. All procedures will be performed sequentially in a same surface by trained operators ([name]), in the same appointment.

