### SDF group

#### Placebo therapy

Individuals will receive sterile water application, as a placebo, maintaining the same steps of resin infiltration technique. Absolute isolation will be simulated just positioning the rubber dam on teeth, without local infiltration anesthesia and clamp.

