On the other hand, we must consider that sequential treatments may influence patients’ perception about the treatment. Because of its sensitivity to light, a light-curing or light curing simulation will have to be applied after the use of SDF. Thus, the sequence has been standardized and our option was to apply the faces scale at the end of all procedures, and not only after the active treatment, despite the latter being ideal. The use of the scale only after active treatment would compromise the blinding, which would be worse. In addition, using the procedures in sequence will make the sessions longer. Therefore, we believe we should discuss our results considering that a session for application of SDF on initial approximal caries lesions would certainly consume less time than will be presented in the results of this trial. A pilot study is ongoing to check the partial times for each approach separately and the influence of each individual treatment and their respective placebos on patient perception.

Finally, we should expect a degree of memory bias, especially a named choice-supportive bias [45] when we checking daily flossing. Actually, children and adolescents, as well their parents/guardians, may be conscious of the correct flossing behavior [46], especially in a study like ours, since they are orientated to act in a specific way during a certain time. Therefore, they could report the daily use of dental floss, regardless of this being the case. This bias could underestimate the actual efficacy of this practice and should be considered when interpreting our findings.

At the end of this study we expect to contribute to point out the option(s) which would be definitely more efficacious/cost-effective than the mechanical removal of biofilm from approximal surface by flossing.

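### Appointment times feeding the cost-efficacy analysis include sham procedures, and no stated rule removes sham time or sham consumables

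*Protocol article*

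**What the plan says.** The abstract states the hypothesis: "Our hypothesis is that SDF is the most cost-efficacious option from all tested interventions". Its methods paragraph names the cost inputs: "Appointments will be timed and costs of materials will be considered to calculate cost-efficacy".

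Under second outcome measurements, "All appointments will be timed by an external examiner". Expected and unexpected visits are counted, and "the procedure performed in each session will be recorded, as well as their respective duration". Materials are priced at average market values and indirect costs are added. A cost-efficacy model is to be proposed later from the efficacy and cost data collected.

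What a session contains is set under random allocation and the three group descriptions. Active and placebo therapies are given in one appointment: "All procedures will be performed sequentially in a same surface by trained operators". In the SDF group, "Individuals will receive sterile water application, as a placebo, maintaining the same steps of resin infiltration technique", but without anaesthesia or clamp. The infiltration group receives a sham SDF application. For controls, "When the active treatment is exclusively flossing, two placebo therapies will be used".

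The Discussion acknowledges that giving the procedures in sequence lengthens the sessions, and that an SDF session "would certainly consume less time than will be presented in the results of this trial". It offers two responses: to discuss the results with this in mind, and an ongoing pilot that measures partial times for each approach.

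**The concern.** Chair time is a cost input, and the sessions being timed contain procedures that exist only for blinding. In practice an SDF patient would not receive a simulated infiltration, and a flossing patient would receive neither sham. If whole-session time enters the cost model, each arm is charged for something outside its own treatment, by a different amount in each arm. Discussing the results afterwards cannot undo a bias that differs between arms.

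The direction is mixed. Against infiltration, the added time hides part of SDF's saving. Against flossing, it hides time that SDF really adds, because the control session is lengthened most. The Discussion concedes only the overstatement for SDF and does not mention the control arm. Yet it justifies having that arm by the need to establish which technique is simplest and most cost-efficacious.

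**Working it through.** The article gives no session time or cost figure to reproduce, so the check adds up the step times it scripts.

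**Inputs, per surface**
- SDF (SDF group, Intervention): 3 min application + 30 s wash, so S = 180 + 30 = 210 s.
- Infiltration (Resin infiltration group, Intervention): 120 s acid + 120 s resin + 40 s cure + 30 s reapplication, so I = 120 + 120 + 40 + 30 = 310 s. Washing, drying, ethanol and the second cure have no stated time, so this is a minimum.
- x: anaesthesia and clamp, done for real only in the infiltration arm. The duration is not stated; 0 to 15 min is assumed.
- Flossing instruction is given in every arm with no stated time. It cancels from differences and is left out.
- Assumption: each sham takes as long as the steps it copies, apart from x.

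**Each arm alone and as timed**

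| Arm | Alone | As timed | Sham time added |
|---|---|---|---|
| SDF | S = 210 s | S + I = 520 s | 310 s |
| Infiltration | I + x = 310 s + x | S + I + x = 520 s + x | 210 s |
| Control | 0 s plus instruction | S + I = 520 s | 520 s |

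**Differences between arms**
- SDF minus control: alone 210 − 0 = 210 s; as timed 520 − 520 = 0 s.
- Infiltration minus SDF: alone (310 + x) − 210 = 100 s + x; as timed (520 + x) − 520 = x.

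**Sensitivity of infiltration versus SDF to the assumed x**

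| x | Difference alone | Difference as timed | Share lost | Ratio alone | Ratio as timed |
|---|---|---|---|---|---|
| 0 min | 100 s | 0 s | 100/100 = 100% | 1.48 | 1.00 |
| 2 min | 220 s | 120 s | 100/220 = 45% | 2.05 | 1.23 |
| 5 min | 400 s | 300 s | 100/400 = 25% | 2.90 | 1.58 |
| 10 min | 700 s | 600 s | 100/700 = 14% | 4.33 | 2.15 |
| 15 min | 1000 s | 900 s | 100/1000 = 10% | 5.76 | 2.73 |

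The SDF-control result does not depend on the particular seconds. If the shams reproduce the steps, both sessions contain the same two sequences and their expected durations are equal whatever each step takes. The infiltration-SDF result does depend on x and on the untimed steps.

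**The case against.** Several counterarguments have force.

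- **Real steps still separate infiltration.** A reader might infer that the shams make procedure time nearly equal in all three arms. The article does not support this. Anaesthesia and clamp are real only in the infiltration arm, and their duration is not given. The timed sessions of infiltration and SDF are equal only if x is zero.
- **Time is one component of cost.** Materials are priced separately and visits are counted. The sham agent is sterile water, whereas infiltration uses a commercial kit, so these costs still differ between arms. A reader might infer that the cost-efficacy answer will be wrong. No cost per minute, material price or cost-efficacy ratio is given, so no change of ranking can be shown.
- **Per-procedure timing may already be intended.** The clause "the procedure performed in each session will be recorded, as well as their respective duration" can be read as a duration for each procedure. The wording is ambiguous. The Discussion's remark about the time the results will show points towards whole-session times, but does not settle it. It is therefore not established that participants already treated have only session totals.
- **The authors have seen the problem, and this is a condensed article.** The inflation of SDF time is disclosed, the pilot is a sensible step, and details of the cost model could sit in a fuller document. But the article does more than omit a detail. It makes appointment time a cost input, says the SDF time to be presented will be too long, and gives discussion as the response. The pilot is not linked to the cost model.

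The seconds are also minimum scripted times. Including instruction and other common steps would bring the ratios closer to 1, without changing the differences those steps share.

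**Conclusion.** The concern holds for the time-based part of cost. Followed as written, the plan times sessions that include shams and states no rule to remove sham time or consumables. On scripted minimum times, the 210 s difference between SDF and control disappears, and that between infiltration and SDF falls from 100 s + x to x. SDF's own time is overstated by about 520/210 = 2.5-fold on scripted steps, and less once common steps are counted. The control arm is affected most, with 520 s added.

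This rests on two assumptions: that shams take as long as the steps they copy, and that whole-session time is what enters the model. If durations are already kept per procedure, what remains is a missing costing rule.

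The size for infiltration versus SDF cannot be fixed without x. The point bears on a stated aim and on the abstract's hypothesis, but not on the clinical primary outcome. It should be corrected before the cost analysis.

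**What to change.** In the section on second outcome measurements, state that:

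1. duration is recorded separately for the active procedure, each placebo and the flossing instruction;
2. the cost model uses only active and common steps, and excludes placebo time and placebo consumables, such as a rubber dam placed only for the simulation;
3. where only whole-session times exist, the pilot's partial times are used in their place, with a sensitivity analysis;
4. whole-session time is reported descriptively only.

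The cost is small. An external examiner already times the appointments, so the first item means a few more stopwatch readings. The pilot is already under way, and the trial status section says recruitment is continuing. The drawback is that any participants already treated without per-procedure times will carry pilot-based values rather than their own, which is why the sensitivity analysis is needed.

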### Independent variables

A structured questionnaire will be answered by the parents/guardians to check the individual characteristics of children/adolescents, such as socioeconomic, behavioral, medical, hygiene, use of fluoride, and dietary factors. One trained and calibrated examiner ([name]) will also assess caries experience using World Health Organization criteria (Decayed, Missing, Filled Surfaces in permanent teeth (DMFS) and DMFS in primary teeth (dmfs)) [29]; visible and disclosed biofilm [30, 31]; gingival papilla status of the approximal surfaces included [32]; and general biofilm by Simplified Oral Hygiene Index [33]. Individual caries risks will be evaluated by Cariogram Software [34] (Figure 2).

**Figure 2 Fig2:**
[figure not shown]
**Sequence of procedures performed for each recruited child**/**adolescent.** *Active and placebo therapies may be performed in different order depending on the group. In the control group, the active treatment is the flossing and two placebo therapies will be performed.

### Follow-up examinations

At baseline, independent variables will be collected for each patient. In addition, for each included surface, the ICDAS and radiographic scores will be registered, as well as the caries activity status.Patients will be assessed after 1, 3, 6, 12, and 24 months. At the 1- and 3-month follow-up the independent variables related to presence of biofilm will be re-evaluated. At other follow-ups (6, 12, and 24 months), direct visual examination of enrolled surfaces will be performed after tooth separation for 48 hours. Moreover, radiographic examination will be performed on the 12- and 24-month follow-up visits (Figure 2). The examinations will be performed as explained in previous sessions.

### Statistical analysis

The intra- and interexaminer reproducibilities in direct visual inspection and radiographic examination will be calculated by the unweighted and weighted Kappa test, depending on the evaluated outcome.

Univariate and multiple multilevel analyses will be used: i) to verify if the used treatment influences on efficacy and cost-efficacy for arresting initial caries lesions and ii) to test the association between different independent variables and treatment efficacy. Caries progression to evident cavities will be the main outcome considered in these cases. If necessary, surrogate outcomes will be used in these analyses. The relative risks and hazard ratios with 95% confidence interval (CI) will be calculated, respectively, after 2-year follow-up and considering all follow-up times. For all multilevel analyses, the surface, the tooth, and the child will be used as levels.

The following independent variables will be tested according to the level: i) surface: visible and disclosed biofilm on the approximal surface; ii) tooth: side; arch [35]; iii) child: age in years; number of daily toothbrushings; who toothbrushes; type of toothpaste; use of dental floss; who flosses; previous visit to a dentist; previous professional topical fluoride application; caries experience (dmfs + DMFS); simplified oral hygiene index [33]; number of active caries lesions in smooth surfaces; individual caries risk; and socioeconomic, behavioral, and dietary factors.

Poisson analysis will be used to assess the association between intervention and patient discomfort and parents’/adolescents’ satisfaction. The prevalence ratio or rate ratio with a 95% CI will be calculated, depending on the outcome considered. If necessary, relevant independent variables will be included for adjustment in the final models.

Interim-analyses will be performed on the primary outcome when 50% have completed 12-month and 24-month follow-up and also, when 100% of patients completed the 12-month follow-up.

The significance level for all analysis will be *P* < 0.05. For all multiples models tested, a level of significance of 0.20 will be considered for the variable entering into the model and a level of 0.05 for remaining in the model.

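### The abstract and the Methods define the primary outcome differently, and an open-ended clause on surrogates leaves room to choose the headline outcome after outcome data have been seen

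*Protocol article*

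**What the plan says.** Three places in the protocol article bear on the primary outcome.

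- Abstract, Methods/design: "Our primary outcome will be caries progression by clinical and radiographic examinations". No threshold of progression is given.
- Primary outcome: "The main outcome considered will be caries progression to evident dentine cavitated caries lesion". The same section then says of other measures: "The progression detected by radiographs or by ICDAS scores transition", together with changes in activity status, "will be considered as possible surrogate outcomes".
- Statistical analysis, on the multilevel models for efficacy and cost-efficacy: "Caries progression to evident cavities will be the main outcome considered in these cases". The next sentence reads: "If necessary, surrogate outcomes will be used in these analyses".

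The Statistical analysis section also says: "Interim-analyses will be performed on the primary outcome when 50% have completed 12-month and 24-month follow-up", and adds a further analysis when all patients have completed 12 months. On the error level it says: "The significance level for all analysis will be" P < 0.05. It attaches relative risks to the 2-year follow-up and hazard ratios to all follow-up times.

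**The concern.** There are two linked problems.

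First, radiographic progression belongs to the primary outcome in the abstract and is only a candidate surrogate in the Methods. The two definitions can count different surfaces as events: a lesion that deepens on the radiograph without cavitating is progression under one and not under the other.

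Second, the sentence on surrogates admits up to three further outcomes into the models that carry the main conclusion. It does not say what would make this necessary, which surrogate would be used, or when and by whom that would be decided.

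The measures are not interchangeable. Surfaces enter at ICDAS 1, 2 or 3, so a score transition may be a single step well short of cavitation. Visual examinations are at 6, 12 and 24 months but radiographs only at 12 and 24, so a time-to-event analysis would rest on different visits.

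If the choice among these outcomes were made with results in view, the reported P value and confidence interval would lose their nominal meaning. A reader of the final report could not tell whether that had happened.

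**Working it through.** **Step 1: the three statements side by side**

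| Place | Primary outcome | Status of radiographic progression |
|---|---|---|
| Abstract | Progression, clinical and radiographic | Part of the primary |
| Primary outcome section | Dentine cavitation | Possible surrogate |
| Statistical analysis section | Evident cavities | Not named; covered by the clause on surrogates |

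The two Methods sections agree with each other. The conflict is between them and the abstract.

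**Step 2: number of candidate outcomes**

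Cavitation, radiographic progression, ICDAS transition and activity change give k = 4.

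**Step 3: the plan's own figure**

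The plan sets 0.05 for every analysis. With one fixed outcome (k = 1), one comparison and one look, the false-positive rate is 1 − (1 − 0.05)^1 = 0.05, as stated.

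**Step 4: worst case under free choice**

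Assume that each of k outcomes is tested two-sided at 0.05 and the most favourable is reported. The plan does not state sidedness, so two-sided is an assumption. For independent outcomes the rate is 1 − (1 − 0.05)^k:

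- k = 2: 1 − 0.95² = 0.0975
- k = 3: 1 − 0.95³ = 0.143
- k = 4: 1 − 0.95⁴ = 0.185

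Outcomes measured on the same surfaces will be correlated. For a common correlation ρ between test statistics, the rate is P(max |Z_j| > 1.96), where the Z_j are jointly normal with mean 0 and variance 1. Simulation with 400,000 draws gives:

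| ρ (assumed) | k = 2 | k = 3 | k = 4 |
|---|---|---|---|
| 0.3 | 0.095 | 0.135 | 0.174 |
| 0.5 | 0.091 | 0.125 | 0.156 |
| 0.7 | 0.084 | 0.109 | 0.130 |
| 0.9 | 0.071 | 0.083 | 0.093 |

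The documents give no correlation, so the range is what matters. For four outcomes it runs from about 9% (ρ = 0.9) to 17% (ρ = 0.3).

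These figures cover one treatment comparison in one of the two parallel studies, at one look. The interim analyses and the several arm comparisons are separate matters and are not included.

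**Step 5: effect on the sample size**

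The stated total follows from the plan's own steps: 86 × 3 = 258; 258 × 1.30 = 335.4, taken as 336; 336 × 1.5 = 504. The Sample size calculation section does not say which outcome its 30% and 20% differences refer to. It therefore does not settle which outcome is primary, and fixing the outcome does not by itself change the 504.

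**The case against.** The strongest reply is that the Methods name one main outcome consistently. On this view the abstract is a loose summary, since the Primary outcome section describes both visual and radiographic examinations, and the surrogates can be read as supplementary. Much of this stands. It narrows the inconsistency to the abstract, and it means the text cannot be said to authorise replacement.

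A second reply is that criteria for supportive outcomes may sit in an analysis plan or full protocol that is not shown. This stands only in part. Detail can be left to another document, but here the article itself publishes an open condition attached to the main efficacy models. That condition has to be withdrawn or bounded wherever the detail sits.

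Third, the error rates in the working assume the least careful use of the clause. A surrogate adopted only because pooled cavitations were few, without sight of between-arm results, would not inflate the error in that way. This stands, and the figures should be read as a worst case.

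A reader might also infer three stronger things, none of which the documents support:

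- **Outcome switching is a stated rule.** The text says surrogates will be used in the analyses, not that they take the place of cavitation.
- **A switch is likely because cavitations will be few.** The Discussion does describe fluoridated water, fluoride toothpaste and regular monitoring. But the plan gives no expected cavitation rate, enrols active lesions, and says that progression tends to be faster in primary teeth and that flossing alone has not been shown to be effective.
- **Comparative interim looks precede the decision on surrogates.** The interim analyses are on the primary outcome, but the text does not call them comparative or unblinded, and it does not date the decision.

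**Conclusion.** The point holds in a limited form. The abstract and the Methods disagree on whether radiographic progression is part of the primary outcome. The clause on surrogates has no criterion and names no measure, so a choice of headline outcome after outcome data have been seen is not excluded.

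The size is a worst-case false-positive rate of about 9% to 17% against a nominal 5%. It rests on four outcomes, two-sided tests at 0.05, one comparison, one look and assumed correlations of 0.9 to 0.3. It describes what the wording allows, not what the investigators intend.

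This should be fixed. It is not a fatal flaw, because the operative sections already agree on cavitation.

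**What to change.** 1. State one primary outcome and one time point in the same words in the abstract, the Primary outcome section and the Statistical analysis section. Cavitation at 24 months is what the Methods already indicate.
2. Delete the sentence that brings in surrogates if necessary.
3. List radiographic progression, ICDAS transition and activity change as pre-specified secondary outcomes, always reported and never able to replace the primary.
4. If the sponsor fears too few cavitations, make any change of primary outcome before between-arm results are seen, using pooled counts only, and document the date and reason.

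The cost is wording in three places. Every outcome is already collected at the planned visits, so no examination or visit is added. The one real downside is losing the freedom to switch later.
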